## Obligation of the investigator regarding safety reporting

All AEs, regardless of seriousness or relationship to the study medication are to be recorded in the Case Record Form. Whenever possible, symptoms will be grouped as a single syndrome or diagnosis. The investigator will specify the date of onset, intensity, action taken with respect to study medication, corrective treatment/therapy given, outcome and his/her opinion as to whether there is a reasonable possibility that the AE was caused by the study medication.

In the case of a SAE the investigator must immediately:

- Ensure appropriate medical care of the study participant and follow-up until clinical recovery is complete
- Inform, in writing, the DMC including a signed and dated copy of the case record form
- Inform the study Sponsor using the appropriate local form (available at <https://intranet.sgul.ac.uk/admin/research/clinic/index.php>)
- In the case of any SAE brought to the attention of the investigator at any time after the cessation of the study medication and considered by him/her to be caused by the study medication with a reasonable probability, this should be reported to the DMC

In the case of an AE, when knowledge of the identity of the study medication is essential for treating the patient, the code for randomisation will be broken. Wherever possible this should be initiated by the DMC. In the event of an emergency an unblinding procedure may be authorised by the investigator. If the blind is broken, the investigator will document the time, date and reason for code breaking in the case record form.

**Laboratory test monitoring**

Abnormalities of laboratory values developing during the study period, or worsening of pre-existing abnormal values, during the duration of the study period will be recorded as AEs.

## Pregnancy

In the unlikely event of pregnancy occurring the study medication will be stopped and the sponsor informed. Follow-up of the pregnancy will be mandatory in all cases until the outcome has been determined. Pregnancy will be recorded as an AE in all cases. It will be qualified as an SAE only if it fulfils criteria.

## Obligations of Sponsor

During the course of the study, the Sponsor will report in an expedited manner all SAEs that are both unexpected and at least reasonably related to the study medication, to the investigators, to the Authorities, and to the Medicines and Healthcare products Regulatory Agency (MHRA) / Local Research Ethics Committee (LREC) as appropriate.

## List of criteria for discontinuation of study medication

The patient may be withdrawn from the study if any of the following events occur:

- Significant intolerance of study medication
- Investigator decides that it is in the best interests of the patient to terminate his/her participation in the study
- Poor patient compliance and/or major protocol deviation
- Patient wishes to terminate his/her participation in the study

The patients may withdraw from the study at any time irrespective of the reason. Given the short nature of the study, temporary discontinuations of study medication are not planned. The reason for medication discontinuation will be documented in the case record form.

## Handling of patients after treatment discontinuation

Patients withdrawn from the study will continue to be followed up according to the study protocol to the scheduled date of study completion, or to recovery or stabilisation of a followed-up AE, whichever comes last. Routine medical and surgical care of withdrawn patients will continue as planned. The investigator will make every effort to contact the patient in the case of a patient not attending a planned review appointment.

## Pregnancy

In the highly unlikely event that a subject becomes pregnant the study medication will be discontinued and the DMC and Sponsor informed. Pregnancy will be recorded as an adverse event in all cases. It will be qualified as an SAE only if it fulfils SAE criteria.

## List of criteria for premature discontinuation of the study

The study may be discontinued prematurely by the Sponsor, the DMC or the Principal Investigator if:

- As a result of the interim analysis or any other event during the study there is doubt as to the risk/benefit ratio
- The results of the trial do not appear to be scientifically convincing to the Sponsor
- The aim of the study has become outdated or is no longer of interest
- There is a breach by the investigator of a fundamental obligation under this agreement, including but not limited to breach of the Study Protocol, breach of the applicable laws and regulations or breach of the ICH guidelines for Good Clinical Practice

In all cases the LREC, MHRA and Health Authority will be informed.

# Study Procedures

## Visit schedule

Subjects will be identified and recruited as described above. The case record form will be completed, vital signs documented, an ECG performed and baseline blood samples taken at the time of the first visit, prior to randomisation. Patients will be reviewed in a private room in the surgical outpatient department.

A second review is planned after seven days of study medication. This semi-structured interview will be conducted in person and a blood test will be taken to check for haematological and biochemical parameters. Any subject who experiences any self-reported adverse events will be reviewed in person at the earliest opportunity.

A review is planned at the end of the two week period of study medication. In addition to a clinical review including recording of vital signs, repeat blood samples will be taken and an ECG performed. A further brief review for the purpose of determining any adverse events that may have occurred after the end of the period of treatment with the study drug will be performed during the operative inpatient stay (or at a relevant timepoint in the case of cancellation of surgery). **A final blood sample will be taken approximately 28 days after the date of surgery, at a routine postoperative clinic appointment.**

Participants will be provided with contact details for the investigators. Additional reviews will be arranged, if necessary, at the participants’ request.

It is anticipated that the study medication will be started fifteen days before the scheduled surgery to co-ordinate the end-of treatment study assessment with the pre-operative admission assessment.

## Treatment group assignation

Subjects recruited to the study will be randomised to receive either artesunate or placebo in equal proportions. Randomisation will be by computer-generated code, supplied in opaque envelopes by the study statistician. Copies of the key to the randomisation codes will be held by the Clinical Trials Pharmacist only. The code will only be broken in exceptional circumstances, when knowledge of the investigational drug is essential for medical treatment of the patient.

## Data collection

Data will be stored in anonymised form in a password-protected database in locked rooms. We will use Filemaker Pro™ as our relational database storage programme. Study documentation will be stored for ten years after the completion of the study.

Basic demographic and clinical information will be gathered at the time of the initial interview and by review of the medical notes if needed. The following information will be recorded for all subjects (see Appendix 2):

- Demographic details: Date of enrolment, age, gender, ethnicity, contact details for participant and GP
- Clinical data: symptomatology, risk factors for development of CRC, weight, height, vital signs
- Findings at endoscopy
- Imaging: findings of ultrasound, CT and/or MRI (performed as clinically indicated)
- Disease staging: TNM staging prior to surgery and definitive histological staging (TNM, Duke’s stage)
- Histology: routine histological grading, apoptosis count and specialist assays (see below)
- Non-study drug treatment: a full record of all non-study drugs taken will be kept
- Study-drug treatment: compliance with study medication, all adverse events, serious or otherwise

The following blood samples will be taken and analysed:

- Baseline: full blood count (FBC), urea and electrolytes, liver function tests (LFT), glucose, carcinoembryonic antigen (CEA)
- Mid treatment: FBC, urea and electrolytes, LFT
- End of treatment: FBC, urea and electrolytes, LFT
- Serum and plasma will be taken at baseline and end of treatment and stored at -80°C for proteomic analysis within one hour of phlebotomy
- Any other blood or clinical sample at any time if deemed necessary by the Investigators in case of a suspected adverse event
- **Peripheral blood mononuclear cells (PBMC) will be taken at baseline, at the end of treatment and after convalescence from surgery.**

Tissue samples will be taken at the time of surgery for analysis as described below.

# Outcome Measures

## Primary outcome measure - efficacy

The primary outcome measure for the treatment response study will be a significant difference in the proportion of cells that exhibit apoptosis between the 2 treatment groups (placebo and artesunate). As CRC is unlikely to exhibit significant apoptosis if untreated, >7% of cells with apoptotic features will be considered significant and consistent with drug effect. As there will be placebo-controlled subjects in this study (who will receive the conventional pre-operative standard of care), the proportion of subjects who have increased proportion of apoptotic cells in artesunate recipients will be compared with those receiving placebo.

The following sample size has been estimated by the statistician using Clinistat:

Estimated sample size for two-sample comparison of proportions

Test Ho: p1 = p2, where p1 is the proportion in population 1

and p2 is the proportion in population 2

Assumptions:

alpha = 0.0500 (two-sided)

power = 0.9000

p1 = 0.0500 (i.e. 1 patient or none will have apoptotic cells in placebo recipients).

p2 = 0.58 (i.e. 7 patients will have apoptotic cells in artesunate recipients).

n2/n1 = 1.00

Estimated required sample sizes:

n1 = 11

n2 = 11

This sample size has the power to detect a difference between apoptosis rates of 18% and 75%. This outcome measure will be scored without knowledge of intervention, as this is a double-blind investigation.

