# Study Objectives

The primary objective of the study is to determine the anticancer effect of oral artesunate in colorectal adenocarcinoma defined as the proportion of malignant cells undergoing apoptosis.

Secondary outcome measures are to establish the tolerability of oral artesunate in colorectal cancer and the effects of artesunate on tumour markers and other clinical endpoints.

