## Other histological assessments

These will be detailed assessments including those of tumour markers and other surface markers in routine use at St. George’s. Biopsies will be assessed specifically for specialised assays, carried out in [name] laboratory (Heidelberg) and will include:

- Determination of apoptosis using TUNEL assay (using a commercially available kits) – this is the primary endpoint of this study
- Immunohistochemical analyses of paraffin-embedded tumor sections with particular assessment of vascular endothelial growth factor (VEGF), *c-myc* status and EGF-receptor status
- Determination of microvessel density
- Proliferative activity (Ki-67 staining)

Material will be obtained at the time of resection of the tumour for routine histological purposes, and surplus material will be used for the histological studies listed. Several small pieces of tumour material (1 mm3) will also be collected into RNA later™ (Trizol), or without preservative and stored at

-70°C or below for expression studies using microarrays, and other genomic analyses.

An aliquot of serum will be stored on admission and just before surgery, for proteomic analyses (carried out at St. George’s). **PBMC typing, and the effect of artesunate on expression of cell surface markers will be assessed.**

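### The plan leaves two rival primary analyses, one continuous and one yes/no, and names no test; the yes/no version it is sized on has about 68% to 82% power at 11 per arm, not 90%

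*Combined protocol and SAP*

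**What the plan says.** Study Objectives gives the anticancer effect as "defined as the proportion of malignant cells undergoing apoptosis". The section Primary outcome measure - efficacy opens in the same vein, with "a significant difference in the proportion of cells that exhibit apoptosis between the 2 treatment groups". Both describe a percentage measured on each tumour.

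The same section then sets a rule, ">7% of cells with apoptotic features will be considered significant and consistent with drug effect", and states that "the proportion of subjects who have increased proportion of apoptotic cells in artesunate recipients will be compared with those receiving placebo". The reference for an increase is not given. Data collection and Other histological assessments take study tissue at surgery, and no pre-treatment apoptosis count is explicitly planned.

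The sample size is for a comparison of two proportions of patients: 5% against 58%, two-sided alpha 0.05, 90% power, 11 per arm. The rates are glossed as "p1 = 0.0500 (i.e. 1 patient or none will have apoptotic cells in placebo recipients" and "p2 = 0.58 (i.e. 7 patients will have apoptotic cells in artesunate recipients". A closing sentence says the same size can detect 18% against 75%.

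Other histological assessments says of the TUNEL assay that "this is the primary endpoint of this study", without a summary measure or threshold. Statistics gives intention to treat and a 5% level, and names no test.

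**The concern.** A continuous comparison of cell percentages and a comparison of responder rates are different analyses with different tests, estimates and power. If the plan does not say which is primary, the more favourable can be reported as such. Blinded scoring protects the measurements but not this choice. The planned efficacy look after ten patients would use the same undefined endpoint.

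The responder version also rests on two unsupported numbers. The only reason offered for 7% is that untreated colorectal cancer is unlikely to show much apoptosis. No reason is offered for a 5% placebo rate. If that rate is wrong, or if the sizing formula is too generous for 11 per arm, the trial has less chance of detecting its target effect than it claims.

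**Working it through.** **Inputs, all from Primary outcome measure - efficacy.** p1 = 0.05, p2 = 0.58; second pair 0.18 and 0.75; two-sided alpha 0.05; power 0.90; 1:1 allocation; 11 per arm.

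**1. The plan's own figure.** Unpooled normal approximation without continuity correction:

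n = (z0.975 + z0.90)² × [p1(1−p1) + p2(1−p2)] / (p1−p2)², with (1.960 + 1.2816)² = 10.507.

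- 5% vs 58%: 10.507 × (0.0475 + 0.2436) / 0.53² = 10.507 × 0.2911 / 0.2809 = 10.89, so 11.
- 18% vs 75%: 10.507 × (0.1476 + 0.1875) / 0.57² = 10.507 × 0.3351 / 0.3249 = 10.84, so 11.

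The figure reproduces. Other two-sided formulas at 90% power for 5% vs 58% give 13 (arcsine), 14 (pooled) and 18 (pooled with continuity correction).

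**2. Actual power at 11 per arm.** Sum the binomial probabilities of all 12 × 12 possible outcomes in which the test rejects at 5%.

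| Placebo vs artesunate | Fisher | Uncorrected chi-square |
|---|---|---|
| 5% vs 58% | 68% | 82% |
| 18% vs 75% | 67% | 82% |
| 10% vs 58% | 52% | 69% |
| 20% vs 58% | 29% | 46% |
| 30% vs 58% | 14% | 27% |

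The largest true type I error at this size is about 1.7% for Fisher and 5.3% for chi-square, so Fisher is conservative and chi-square slightly liberal. Neither reaches 90% at either stated pair.

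**3. The uncut percentage.** The documents give no SD or distribution, so two assumed models bracket the answer.

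*Location shift.* Suppose the percentages, on some monotone scale, are normal with equal SD, and the cut yields the stated rates. The shift is z(0.58) − z(0.05) = 0.202 + 1.645 = 1.85 SD, or z(0.75) − z(0.18) = 0.674 + 0.915 = 1.59 SD. The exact Wilcoxon test (true alpha 0.047) has simulated power of about 98% and 93%. That is about 10 to 15 points above chi-square and 26 to 30 above Fisher.

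*All-or-none.* Suppose patients either respond or do not, and the cut separates them cleanly. Wilcoxon power is about 59–61% for 5% vs 58% and 66–72% for 18% vs 75%, varying with the spread within each group. (The lower figures take non-responders uniform from 0 to 7% and responders uniform from 7 to 20%.) For the first pair this is below Fisher's 68% and well below chi-square's 82%.

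**4. Do the two analyses disagree?** In the shift simulations, Wilcoxon on the percentages and the binary test on the cut gave opposite significance verdicts in about 13% (chi-square, 18% vs 75%) to 30% (Fisher, 5% vs 58%) of trials.

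**The case against.** The primary outcome section can be read as one chain: measure the percentage, call a tumour positive above 7%, compare the proportions of positive patients. On that reading the sizing fits, an increase means exceeding 7%, TUNEL is merely the assay, and the objective is not an analysis. This stands in part. It reduces the candidates to two, so a reader who counts several rival primaries goes too far. It does not dispose of the opening sentence, which defines the outcome as a difference in cell proportions, and no test is named under either reading. The sizing lines do not repeat the 7% figure, so linking them to that cut is the natural reading rather than a statement in the text.

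A reader might infer that cutting at 7% simply throws power away. The documents do not support that. The gain from the uncut percentage appears under a shift and reverses under an all-or-none response, and the plan's gloss about patients who will or will not have apoptotic cells is, if anything, nearer the latter. About half of the 98% against 68% contrast is Fisher's conservatism, not the cut. Less conservative binary tests reach 77% (Boschloo) or 82% (exact unconditional test on the pooled z) at 5% vs 58%. By the latter test, power at placebo rates of 10%, 20% and 30% is about 68%, 42% and 23%: higher than Fisher's, but still falling steeply.

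It is also fair that the plan contemplates a higher placebo rate, 18%. It does so only with an artesunate rate of 75%. Finally, seven patients of 11 is 64%, whereas 58% matches 7 of 12; at 64% against 5%, chi-square power is about 89%.

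**Conclusion.** The concern holds in this form: two primary analyses are left open, no test is named, and the 7% cut and 5% placebo rate are unsupported. This part needs no distributional assumption.

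The binary comparison has about 68% (Fisher) or 82% (chi-square) power for both stated rate pairs, against 90% claimed. With artesunate at 58%, a placebo rate of 10% already brings that down to 52% or 69%. These figures assume all 22 patients are evaluable.

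A reader might take the shortfall as a calculation error. It is not one: 11 per arm follows from a recognised formula that is optimistic at this size. The effect of the cut on power is conditional, from a gain of 10 to 30 points for the uncut percentage under a shift to a loss under an all-or-none response. Nor do the documents show any intention to choose the analysis late; they merely fail to prevent it.

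**What to change.** Before any unblinded data are seen, including the interim look:

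- Name one primary variable: the TUNEL percentage of apoptotic tumour cells in the resection specimen, compared between arms by exact Wilcoxon rank-sum test at two-sided 5%, with the Hodges-Lehmann difference and 95% CI.
- Keep >7% as a prespecified supportive responder analysis, with a named test and a risk difference with exact CI. Give the basis for the cut, or say that it is a convention.
- Delete the competing wording in the primary outcome section, and make the objective and the histology section agree with it.
- Restate the power for the chosen test, with the assumed distribution or rates and a range of placebo rates.

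If the sponsor prefers the responder endpoint as primary, that also removes the ambiguity, provided it is defined once, the test is named, and the cut and placebo rate are justified.

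The cost is protocol and SAP wording; no new patients, samples or assays are needed. The downside is that the rank test has less power than a responder test if the effect is truly all-or-none.

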# Study Design

This will be a Phase I randomised placebo-controlled double-blind trial of artesunate given orally to patients with histologically confirmed CRC who will receive treatment with curative intent. The study will involve 22 patients randomly assigned to receive artesunate or placebo. The overall study duration will be 14 days. An interim efficacy analysis is planned after the first ten patients have completed the study.

A Data Monitoring Committee (DMC) will supervise the study. The primary role of the DMC is to protect the safety of the patients participating in the study by reviewing the safety information. Clear criteria for terminating the study prematurely are given. The DMC is composed of three individuals, an individual with expertise in the conduct of drug trials involving artesunate, a statistician and a colorectal surgeon with a specialist knowledge of the management of colorectal cancer.

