## Statistics

All analyses will be made on an intention to treat basis. Statistical significance will be assumed at a 5% level.

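### The 90% power stated for 11 patients per arm comes from an unpooled large-sample formula; no test is named, and exact power for 5% vs 58% is about 68% (Fisher) to 82% (Pearson)

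*Combined protocol and SAP*

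**What the plan says.** Under Study Design, the total is fixed: "The study will involve 22 patients randomly assigned to receive artesunate or placebo".

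Under Primary outcome measure - efficacy, the calculation is described only as "Estimated sample size for two-sample comparison of proportions". Its inputs are "alpha = 0.0500 (two-sided"), power 0.9000, 1:1 allocation, "p1 = 0.0500 (i.e. 1 patient or none will have apoptotic cells in placebo recipients"), and "p2 = 0.58 (i.e. 7 patients will have apoptotic cells in artesunate recipients"). The output is 11 per arm. One further sentence follows: "This sample size has the power to detect a difference between apoptosis rates of 18% and 75" per cent. It gives no power level.

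The comparison being sized is of patients: "the proportion of subjects who have increased proportion of apoptotic cells in artesunate recipients will be compared with those receiving placebo". Neither the sample-size formula nor the analysis test is named. The Statistics section gives only the intention-to-treat basis and the level: "Statistical significance will be assumed at a 5% level".

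**The concern.** Sample-size formulas for two proportions rest on a normal approximation. Here the expected number of placebo responders is 11 × 0.05 = 0.55, so the approximation has little to stand on, and the common formulas disagree noticeably. The plan reports the result of one of them as the power of the trial without saying which test will be used.

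What is at stake is the chance of missing the effect the trial was planned around, a difference of 53 percentage points. On the stated figure that chance is 10%. Under Pearson or Fisher it is 18% or 32%. The unnamed test also matters for individual results: with 1/11 placebo and 6/11 artesunate responders, Pearson is significant at 5% and Fisher is not (p = 0.063).

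**Working it through.** **Inputs** (all from the primary-outcome section): two-sided alpha 0.05 (z = 1.960), power 0.90 (z = 1.2816), p1 = 0.05, p2 = 0.58, 11 per arm. Second pair: 0.18 vs 0.75.

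**1. Reproducing the plan's 11.** Unpooled formula: n = (1.960 + 1.2816)² × [p1(1−p1) + p2(1−p2)] / (p2−p1)².

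- 5% vs 58%: 10.507 × (0.0475 + 0.2436) / 0.53² = 10.507 × 0.2911 / 0.2809 = 10.89, so 11. Approximate power at 11 is 90.3%.
- 18% vs 75%: 10.507 × (0.1476 + 0.1875) / 0.57² = 10.507 × 0.3351 / 0.3249 = 10.84, so 11. Approximate power at 11 is 90.4%.

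The plan's figure is therefore reproduced.

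**2. Other two-sided formulas, 5% vs 58%.**

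- Pooled: mean rate 0.315, so n = (1.960 × √0.43155 + 1.2816 × √0.2911)² / 0.2809 = 13.94, so 14. At 11 per arm this formula gives 80.8% power.
- Pooled with continuity correction: 17.5, so 18.
- Arcsine: 12.82, so 13. At 11 per arm it gives 85.2% power.

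Of the two-sided formulas tried, only the unpooled one gives 11 for 90% power.

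**3. Exact power at 11 per arm.** This treats the two responder counts as independent binomials, enumerates all 12 × 12 outcomes and adds the probability of those the test declares significant. For 5% vs 58%, the chance of 0, 1, 2 or 3 placebo responders is 0.5688, 0.3293, 0.0867 and 0.0137.

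- Fisher needs at least 5, 7, 8 or 9 artesunate responders respectively: 0.5688 × 0.8740 + 0.3293 × 0.4777 + 0.0867 × 0.2510 + 0.0137 × 0.0945 = 0.678.
- Pearson needs at least 4, 6, 7 or 8: 0.5688 × 0.9601 + 0.3293 × 0.7076 + 0.0867 × 0.4777 + 0.0137 × 0.2510 = 0.824.

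| Test | 5% vs 58% | 18% vs 75% | Largest true type I error |
|---|---|---|---|
| Fisher's exact | 67.8% | 67.4% | 1.7% |
| Boschloo | 77.3% | 77.3% | within 5% by construction |
| Uncorrected Pearson | 82.4% | 82.5% | 5.3% |
| Unpooled Wald | 89.7% | 83.3% | 9.1% |

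Barnard's test, which also holds the level by construction, gives 82.2% for 5% vs 58%. Yates-corrected chi-square matches Fisher at 67.8%.

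**4. The patient count.** 7/11 = 63.6% and 7/12 = 58.3%, so the gloss fits 12 per arm and not 11. Conversely, 0.58 × 11 = 6.4 patients. With p2 = 7/11 and p1 = 0.05, exact power at 11 per arm is 77.8% (Fisher) or 89.3% (Pearson).

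**5. What 90% would need.** For 5% vs 58%, Fisher first reaches 90% at 17 per arm (91.7%); 16 per arm gives 89.2%.

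**The case against.** The strongest reply is that nothing was miscalculated. A reader might infer an arithmetic error, but the documents do not support that: 11 per arm at 90% follows from a standard formula applied to the stated inputs. This stands. The weakness is the choice of approximation at this size.

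A reader might also infer that the real power is 68% to 82%. Because no test is named, the plan has no single real power. Exact values for 5% vs 58% run from 67.8% to 89.7% across the tests examined. Fisher, at the low end, is very conservative here. The Wald test at the high end is a weak defence of the 90%. Its type I error is 1.7% if both rates are 5%, but it rises to 7.7% at a common rate of 30% and 9.1% at 20%. Equally, the plan never says it will use Wald, so that inflation is not a defect of the plan.

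A third tempting reading is that the plan claims 90% for 18% vs 75%. The sentence gives no level. It follows directly on a 90% calculation and matches 90% by the same formula, but 11 per arm is also what the pooled formula gives for that pair at 80% power (10.8). The sentence is ambiguous and not shown to be false.

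The patient-count mismatch also cuts partly in the plan's favour: taking 7 of 11 literally brings Pearson to within a point of 90%.

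Finally, overstated planning power biases no estimate and does not inflate type I error, and nothing in the documents says how a null result would be presented. This limits the harm. It does not make the stated 90% a usable description of the design.

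**Conclusion.** The concern holds in this form: 90% power for 5% vs 58% with 11 per arm depends on the unpooled large-sample formula, and none of the tests examined that keep the 5% level, or come close to it, attains it. Depending on the test, exact power is about 68% (Fisher), 77% (Boschloo) or 82% (Pearson, whose true level marginally exceeds 5%). That is a shortfall of roughly 8 to 22 percentage points. If the 18% vs 75% sentence is read as also claiming 90%, its exact power is 67% (Fisher) to 83% (Wald), so no test in the table reaches 90% for that pair. The inconsistency between 0.58 and 7 patients of 11 stands whichever test is chosen.

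These figures assume independent binomial counts, all 22 patients evaluable, and the comparison of responding patients as the primary analysis. The section also words the outcome as a proportion of cells; no variance is given for that, so its power cannot be computed from the documents.

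**What to change.** Keep 22 patients and change the wording of the primary-outcome and Statistics sections:

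- Name the primary test for the comparison of responders.
- Replace the power entry of 0.9000 with that test's exact power at 11 per arm for 5% vs 58%, for example 68% for Fisher's exact test or 77% for Boschloo's test.
- State the power level for 18% vs 75% with the same test (Fisher 67%, Boschloo 77%).
- Make p2 agree with the patient count. Either keep 0.58 and correct the gloss, or set p2 to 7/11 and restate the power (Fisher 78%, Pearson 89%).

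The cost is a text amendment and a less favourable stated power; recruitment does not change. Holding to 90% with Fisher's test would instead take 17 per arm, 34 in total, which is 12 more patients.
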